#### Blood sampling

Up to 15 ABG samples will be taken. Samples will be discarded at the end of the laboratory session into clinical waste and no blood will be retained by the study.

At the end of the study visit, the arterial line will be removed and firm pressure applied to the site until haemostasis is achieved. A sterile dressing will be applied and advice given to the participant on action to take if any bleeding occurs.

### Facilities and research staff

#### Facilities

All study visits will occur in the Cardiovascular Clinical Research Facility, Level 1 Oxford Heart Centre, John Radcliffe Hospital, [name].

#### Roles and responsibilities

Each study visit day will be staffed by one senior anaesthetist, four clinical researchers and one engineer. Roles during the study visit are defined in table 3.

**Table 3 T3:** Research team roles

Professional	Role in study	Description of responsibilities
Senior anaesthetist	Medical cover	Conduct medical screening. Ensure participant safety throughout the study. Inserting/removing radial arterial line. Operating the hypoxicator equipment. Taking ABG samples from arterial line.
Researcher 1	Devices and time-stamping	Ensure correct positioning of all involved devices. Ensure data is being recorded from all monitors. Time-stamping of study activities and ABGs. Troubleshoot any device-related issues throughout.
Researcher 2	ABG processing	Collect and process the ABG. Identify ABG report with correct activity (eg, tapping, tablet, 95%). Discard the blood sample.
Researcher 3	Participant activities and instructions	Explain activities to participants. Giving instructions and guide participants through movement phase activities. Respiratory rate manual count at ABG time points. FiO_2_ manual record at ABG time points in the hypoxia phase.
Researcher 4	Support/backup	Manually record the time ABGs are drawn. Complement/assist any required activities. Responsible for oversight and detection of any suboptimal activities/conditions.
Engineer	Data monitoring	Monitors procedures and real time data quality. Double checks devices. Ensures reliable data acquisition throughout.

ABG, arterial blood gas; FiO_2_, fraction of inspired oxygen.

## Data collection and management

### Devices

To ensure correct time-stamping, Researcher 1 will verify all devices, tablets and laptops are connected to the same network. The time and date will be set to Greenwich Mean Time Zone (GMT) or British Summer Time as appropriate. The time will be verified to be within a tolerance of ±2 s and documented in the case report form (CRF):

AMDsVital Connec, VitalPatch^®^: Single-use (120 hours), adhesive, wireless, waterproof patch that measures heart rate and respiratory rate via a single-lead ECG. Other parameters include three axis motion sensor and skin-temperature sensors.Viatom Technology, CheckMe^™^ O2: Wrist-worn wireless pulse oximeter, measuring pulse rate and percentage Oxygen saturation (SpO2) via transmittance photoplethysmography (PPG) using a ring-style sensor. Other parameters include a motion sensor.Wavelet Health, USA, Wavelet wristband: Wireless wrist-worn pulse oximeter using reflectance PPG to measure pulse rate and percentage Oxygen saturation (SpO2). Other parameters include 3-axis motion sensor and gyroscope.Shenzhen Creative Industry, AP-20: Wrist-worn wireless pulse oximeter, measuring pulse rate and percentage Oxygen (SpO2) via transmittance PPG using a finger-tip style sensor. Other parameters include estimation of respiratory rate using the airflow signal collected from a supplied nasal cannula (attached to an airflow sensor in the device); and 3-axis motion sensor.Nonin Medical, WristOX2 3150 BLE: Wrist-worn wireless pulse oximeter, measuring pulse rate and percentage of Oxygen (SpO2) via transmittance PPG with finger-tip style sensor.Clinical standard:Philips Monitor MX450 and extraction software (ixTrend 2.1):Gold standard:ABGs: The assigned person will manually record the GMT time when each ABG is taken. The ABG processing time will also be recorded as part of the automatic report. The ABGs will be analysed using a Radiometer ABL90 Flex blood gas analyser.

An electronic system, developed in-house, comprising a vital signs data collection application (app) running on Android tablets, and a web-application (administrated by the research group) will allow:

the registration of the participant study number, centralised in the web-application, via the app.the collection of data from one patch (VitalPatch^®^) and one pulse-oximeter (AP-20, CheckMeO2^™^ and WristOX2 3150), via Bluetooth Low-energy, and their storage into files in a tablet.the upload of the files from the tablet to the web-application server (via HTTPS) within 24 hours of the end of each session.the electronic recording of the time-stamping of the activities in each phase of the study session (by researcher 1), that is:
**Movement phase:** Normoxia/Sit to Stand/Tapping/Rubbing/Drinking/Turning/Tablet.
**Hypoxia phase:** 95%/90%/87%/85%/83%/80% SpO2 levels.

A total of 3 tablets will be used to collect data from the VitalPatch^®^, CheckMe^™^ O2, WristOX2 3150 BLE and the AP-20. Wavelet Health’s electronic system will be used to collect data for the Wavelet device.

### Collected data

The following data will be collected for each participant:

Demographic data: including age, sex, height, weight, skin type (Fitzpatrick scale), baseline heart rate and SaO_2_ at start of test (using gold standard ABG measurements).For oxygen saturation, sampled at normoxia and each level of induced hypoxia:
**Gold standard reference:** ABGs (intermittent samples).
**Clinical standard reference:** Standard care pulse oximeter (continuous data).
**Devices under test**: Up to four pulse oximeters (continuous data).For pulse rate, sampled at normoxia and each level of induced hypoxia:
**Gold standard reference:** Arterial line trace (continuous data).
**Clinical standard reference:** Standard care pulse oximeter (continuous data).
**Devices under test**: Up to four pulse oximeters (continuous data).For heart rate, sampled at normoxia and each level of induced hypoxia:
**Gold standard reference and clinical standard reference**: Standard care 3-lead ECG (continuous data).
**Devices under test:** Chest patch (continuous data).For respiratory rate, sampled at normoxia and each level of induced hypoxia:
**Gold standard reference**: Capnography (continuous data).
**Clinical standard reference**: Manual respiratory rate per minute counting (intermittent samples, done at the same time as the ABG sampling).
**Devices under test:** Chest patch (continuous data).

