#### Arterial line insertion

After confirmation of eligibility, an arterial line will be inserted into the non-dominant radial artery of each participant on the day of the study visit under local anaesthesia.

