**Figure 1 F1:**
[figure not shown]
Devices placement example (dominant hand, combination 3).

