#### Finger probe position randomisation

Up to three study device finger probes will be worn, in addition to the ‘clinical standard’ reference bedside monitor finger probe. The CheckMe^™^ O2+ will always be worn on the thumb as per manufacturer recommendation.^10^ To ensure parity of testing, the position of the other three finger probes on the second, third and fourth fingers will be randomised (using https://www.random.org/) per study visit day, ensuring an even distribution of placement, as per table 1).

**Table 1 T1:** Device combinations

Devices placement	Combination 1 (n=10)	Combination 2 (n=10)	Combination 3 (n=10)
Chest	VitalPatch^®^	VitalPatch^®^	VitalPatch^®^
Wrist	Wavelet	Wavelet	Wavelet
1st (thumb)	CheckMe^™^ O2+	CheckMe^™^ O2+	CheckMe^™^ O2+
2nd (index finger)	Philips monitor (MX450)	WristOX2 3150 BLE	AP-20
3rd (middle finger)	AP-20	Philips monitor (MX450)	WristOX2 3150 BLE
4th (ring finger)	WristOX2 3150 BLE	AP-20	Philips monitor (MX450)

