#### Stage 1: movement phase

During the movement phase, participants will be seated in a chair and asked to complete a series of consecutive standardised movements, as detailed in table 2. An ABG and manual (counted) respiratory rate will be taken at the end of each movement.

**Table 2 T2:** Standardised movements to be tested

Movement	Task
Standing from chair using arms to push up/sit down	20x repetitions.
Tapping	Volunteer to tap a surface with all test side fingers simultaneously at the speed of a metronome set at 100 bpm for 2 min.
Rubbing	Volunteer to complete a sideways rubbing movement with all test side fingers simultaneously at the speed of a metronome set at 100 bpm for 2 min.
Drinking from plastic cup	20 x lift/drink/put down.
Turning page	50x page turns.
Using tablet	As per protocoled instructions (online supplementary file 2).

10.1136/bmjopen-2019-034404.supp2Supplementary data

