### Outcome analysis

We will analyse the outcomes on all the participants from whom we collected the data. The accuracy will be compared with the respective reference pulse oximeter. Where paired readings exist (device with clinical or gold standard), they will be included in the analysis. Device readings with no paired clinical or gold standard will be excluded from the analysis.

Primary outcome measure: Sensitivity and specificity for detecting hypoxia at each level ≤90%): The analysis plan detailed above will provide data on correlation of each device with ‘gold standard’ arterial measurements, and their accuracy for the detection of hypoxaemia: The output of this analysis will allow selection of the devices which correlate most closely to the ‘gold standard’ measurements, and provide the highest performance in the detection of hypoxaemia.

Secondary outcome measure: Correlation of device outputs, that is, HR, RR, PR and SpO2, with ECG derived HR, capnography derived RR, arterial blood pulse rate and pulse oximetry, respectively, during movement:

The analysis plan detailed above will provide data on correlation of each device with ‘gold standard’ arterial measurements during protocolised movement tests. The output of this analysis will allow selection of the devices which correlate most closely to the ‘gold standard’ measurements.

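### During movement, the bedside pulse-rate reference shares the tested hand's motion and the arterial-line arm is loaded in one of six tasks; the ECG rate already recorded should be a second reference

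*Protocol article*

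**What the plan says.** All references are to the Protocol article.

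- **Pulse-rate references.** Collected data gives the gold standard as "Arterial line trace (continuous data" and the clinical standard as "Standard care pulse oximeter (continuous data". That list speaks of normoxia and the hypoxia levels. For movement, the secondary outcome in Outcome analysis pairs pulse rate with the arterial signal: "arterial blood pulse rate and pulse oximetry, respectively, during movement".
- **ECG.** The 3-lead ECG is recorded continuously. It is the heart-rate reference, compared only with the chest patch, and Outcome analysis keeps it as the heart-rate reference during movement. It is not assigned to pulse rate.
- **Where the references sit.** Under Arterial line insertion, "an arterial line will be inserted into the non-dominant radial artery of each participant". Under Finger probe position randomisation, "the position of the other three finger probes on the second, third and fourth fingers will be randomised", and one of those three probes is the bedside monitor's (Table 1). The Figure 1 legend reads "Devices placement example (dominant hand, combination 3".
- **Movements (Table 2).** One task is "Standing from chair using arms to push up/sit down", 20 repetitions. For tapping the text is "Volunteer to tap a surface with all test side fingers simultaneously", and rubbing is limited to the test side in the same way. No hand is given for drinking or page turning, and the tablet task is in a supplement that is not shown.
- **Analysis.** A_rms, bias and precision are defined for SpO2 and carried over unchanged to pulse rate.

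**The concern.** A movement test needs a reference that the movement does not disturb. The bedside probe is the same kind of sensor as the finger-probe devices and is on the same hand. The Introduction itself cites work in which motion impaired four non-ambulatory pulse oximeters. The arterial trace is better placed, but the cannulated arm takes load when the participant pushes up from the chair.

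The agreement formulas have no term for reference error, so any disturbance of the reference appears as device disagreement or, if device and reference share it, as false agreement. Outcome analysis uses these results to select devices, so both the absolute pulse-rate accuracy during movement and the comparison between devices are at stake.

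**Working it through.** **1. Exposure of each reference over the six tasks in Table 2**

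| Task | Arterial line (non-dominant arm) | Bedside probe |
|---|---|---|
| Sit-to-stand | loaded (arms, plural) | on device hand |
| Tapping | spared if devices are on the dominant hand | on moving hand |
| Rubbing | spared if devices are on the dominant hand | on moving hand |
| Drinking | hand not stated | on device hand |
| Page turning | hand not stated | on device hand |
| Tablet | instructions not shown | on device hand |

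The arterial reference is therefore documented as exposed in 1 task, spared in 2 on one condition, and unspecified in 3. The bedside probe moves whenever the device hand moves.

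**2. How reference error enters A_rms**

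Let d be the device's root-mean-square error against the true rate, r that of the reference, and ρ their correlation, with errors averaging zero. The plan's A_rms is computed on the difference of the two errors, so

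observed A_rms = √(d² + r² − 2ρdr).

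The documents give no value for d, r or ρ; those below are assumptions.

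**3. Arterial trace in sit-to-stand, independent errors (ρ = 0), d = 3 bpm**

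- r = 1: √(9 + 1) = 3.16
- r = 3: √(9 + 9) = 4.24
- r = 5: √(9 + 25) = 5.83

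Pooled over six equally weighted tasks with only sit-to-stand disturbed, A_rms = √(d² + r²/6):

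- r = 1: √(9 + 0.17) = 3.03
- r = 3: √(9 + 1.5) = 3.24
- r = 5: √(9 + 4.17) = 3.63

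**4. Bedside probe on the same hand, d = r = 3 bpm**

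- ρ = 0: √18 = 4.24
- ρ = 0.5: √(18 − 9) = 3.00
- ρ = 0.8: √(18 − 14.4) = 1.90

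Observed A_rms falls below the true device error whenever r < 2ρd. Tapping and rubbing to a 100 bpm metronome are a plausible source of shared artefact.

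**5. Range.** Over d = 2 to 5, r = 1 to 5 and ρ = 0 to 0.8, observed A_rms runs from 1.26 (d = r = 2, ρ = 0.8) to 7.07 (d = r = 5, ρ = 0). With r = 0 it equals d.

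**6. Bias.** The plan's B is the mean device error minus the mean reference error. A systematic shift in the reference passes straight into B with its sign reversed.

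**The case against.** **The layout protects the gold standard.** A reader might infer that both references are exposed throughout movement. The documents do not support that: the line is in the non-dominant arm, the placement example shows the dominant hand, and tapping and rubbing are test-side only. This stands, and it confines the documented arterial exposure to sit-to-stand. The protection rests on a figure legend that is only an example.

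**Sampling may fall after the effort.** The blood gas is taken at the end of each movement, and one sampling method uses that time point where relevant. This may spare single-point readings. It does not settle the 5–30 s windows, whose position the article does not give and may leave to the full plan.

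**No substitution rule is written.** A reader might infer that the bedside probe replaces a lost arterial trace. Outcome analysis only includes pairs with either standard. It does not say that one stands in for the other, and Data quality and completeness requires both references for a complete data set and a visual audit. What remains is that a pair with only the bedside probe still counts, with no caution for movement.

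**Reference error need not count against the devices.** Step 4 shows that shared artefact can flatter them. Independent error in a common reference also adds equally to each device's expected squared error, so it does not shift their expected ranking. Both points stand. Reported accuracy is still inflated in that case, and devices that share the probe's artefact to different degrees can be ranked wrongly.

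**The ECG is unproven.** Nothing in the documents shows it to be free of artefact during a push-up from a chair, and matching pulse rate to an arterial pulse is a consistent like-for-like choice. This is why the ECG should be added and the arterial trace kept. The plan already relies on the ECG for heart rate during movement.

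**Conclusion.** The point holds as a limited, inexpensive improvement. The clinical pulse-rate reference shares the tested hand's motion, the arterial-line arm is loaded in at least one of six tasks, and a recorded signal that depends on neither the wrist nor the fingers is not used for pulse rate.

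Movement-phase pulse-rate agreement can therefore be distorted either way. At an assumed true device error of 3 bpm, the arterial reference would give 3.2 to 5.8 bpm in sit-to-stand and 3.03 to 3.63 bpm pooled, if its independent error were 1 to 5 bpm. The same-hand probe could give 1.9 bpm if errors were equal and correlated at 0.8. These sizes rest wholly on the assumed errors; the direction and the mechanism rest on the documents.

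A much larger effect is tempting to claim: a 10 bpm reference error would give √(100 + 9) = 10.4 bpm in one task. No figure in the documents supports an error of that size. The primary hypoxia outcome and the SpO2 analyses are not touched by this point.

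**What to change.** In Collected data and Outcome analysis, state for the movement phase that:

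1. the arterial trace remains the gold standard for pulse rate;
2. the 3-lead ECG rate is a second pulse-rate reference in all six tasks, with A_rms and bias reported against both, and serves as the reference where the arterial trace is unusable;
3. pairs whose only reference is the same-hand bedside probe may be described but do not support conclusions on pulse-rate accuracy during movement.

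Agreement between the arterial and ECG rates, by task, would then show how much of the disagreement could come from the references.

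The cost is a few sentences and one repeated analysis; no new equipment or participant burden is needed because the ECG is already recorded. The downsides are that ECG rate and pulse rate can differ with ectopic beats, which should be rare in healthy volunteers, and that the ECG may itself carry some motion artefact.

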### Safety testing and calibration

Philips MX450, ABG machines, hypoxicator, all tablets and chargers were subjected to clinical safety testing by either the Department of Engineering Science, University of Oxford or by the Clinical Engineering team at the Oxford University Hospitals NHS Foundation Trust (OUHFT). ABG analysers are maintained and calibrated by the Clinical Measurements team at the OUHFT.

### Data quality and completeness

Manually entered data (eg, ABG data, RR count, etc) will be subject to a 10% data validation check.

To ensure correct time-stamping, all ABG collection times will be recorded both using the vHDU app and manually recorded time (hh:mm:ss). Each participant AMD, gold and clinical standard, and time-stamp data will be plotted and audited visually up to 1 week after participation to assess data completeness. Each participant dataset will be deemed complete if there are test device data to answer either the primary or secondary objective, including both gold standard and clinical standard reference data.

## Analysis

For continuous data we will sample by two methods: (1) simultaneous single data points, (corresponding to the time of ABG sampling where relevant) and; (2) by selecting sampling windows of 5–30 s and comparing data for each device. Data points will be recorded across device time-stamps to ensure accuracy of comparisons.

In accordance with the international standard of pulse oximeter equipment validation (ISO 80601-2-61:2019), the accuracy of the SpO2 measurement will be stated in terms of the root-mean-square (rms) difference between measured values (devices under test) (SpO2i) and reference values (gold standard arterial line and clinical standard) (SRi), as given by:

$$A_{rms}=\sqrt{\frac{\sum_{i=1}^{n}{\left({SpO}_{2i}-S_{Ri}\right)}^{2}}{n}}$$

We will also compute the bias between gold standard, clinical standard and each device under test:

$$B=\frac{\sum_{i=1}^{n}\left({SpO}_{2i}-S_{Ri}\right)}{n}$$

and the precision:

$$s_{res}=\sqrt{\frac{\sum_{i=1}^{n}{\left({SpO}_{2i}-{SpO}_{2fit,i}\right)}^{2}}{\left(n-2\right)}}$$

where SpO2fit is the value of the fitted curve corresponding to the ‘i’th reference value. Simple statistics about the difference among measurements (mean, SD, percentiles, Bland-Altman plots) will be provided for the all the devices under analysis. Identical statistical methods will be applied to assess the agreement between the estimation of the (i) pulse rate from the pulse oximeters, and of the (ii) heart rate and (iii) respiratory rate from the patch, and the corresponding reference measurements.

The performance of each pulse oximeter in detecting hypoxaemia (at each level ≤90%) will be assessed by reporting the optimal sensitivity and specificity pair, identified via Receiver-Operating Characteristic curves.^7 12^

Descriptive statistics will be also computed per participant, per skin type and with and without movement artefacts.

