### Study objectives

Primary objective: To determine the specificity and sensitivity of currently available ambulatory vital signs monitoring equipment for the detection of hypoxia.

Secondary objective: To determine the effect of movement on data acquisition by currently available ambulatory vital signs monitoring equipment.

These objectives will be assessed by comparing continuous peripheral oxygen saturations, pulse rate, heart rate and respiratory rate data from each AM with arterial blood oxygen saturation measured through arterial blood sampling, pulse rate derived from the arterial blood signal, heart rate derived from standard care 3-lead ECG, and respiratory rate derived from capnography and manual counting.

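### Patch respiratory rate is sampled at one point or over 5–30 s but compared with a manual per-minute count, so the patch-versus-manual agreement figures can include error that is not the patch's.

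*Protocol article*

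**What the plan says.** The Analysis section of the protocol article gives two ways of sampling continuous data. One is "simultaneous single data points, (corresponding to the time of ABG sampling where relevant". The other is "by selecting sampling windows of 5–30 s and comparing data for each device". No separate rule is given for RR. The same section continues: "Identical statistical methods will be applied to assess the agreement between the estimation of the (i) pulse rate from the pulse oximeters", and it extends this to heart rate and RR from the patch against their references.

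RR has two references. Study objectives names "respiratory rate derived from capnography and manual counting". Collected data makes the gold standard "Capnography (continuous data)" and the clinical standard "Manual respiratory rate per minute counting (intermittent samples, done at the same time as the ABG sampling)". The device under test for RR is the "Chest patch (continuous data)". For the movement phase, Stage 1 states: "An ABG and manual (counted) respiratory rate will be taken at the end of each movement".

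Outcome analysis keeps every device reading that is paired with either standard, so the patch-versus-manual comparison will be made. The secondary outcome in that section, however, names capnography as the RR comparator during movement and does not name the manual count.

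**The concern.** The sampling rule suits SpO2 held on a plateau and beat-rate signals, because a few seconds contain enough information. Breathing is slower. The observer reports an average over the counting period, while the rule takes the patch value from an instant or from at most half a minute. If the observer counts for a full minute, the two numbers describe different stretches of breathing even when both are right.

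The difference between patch and count then has three parts: true patch error, breath-to-breath variation, and any trend in RR during the count. Only the first is a property of the device. The statistics against the clinical standard (bias, A_rms, limits of agreement, correlation) would charge all three to the patch, which is the only RR device that the plan assesses. A falling RR after exertion would appear as positive bias and could be taken for a movement effect.

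**Working it through.** The article states no figure for RR agreement, so there is none to reproduce. The check asks how an error-free patch would score.

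**Inputs from the article.** Single point or 5–30 s; manual per-minute count at ABG time, and in Stage 1 at the end of each movement.

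**Assumed, because the article does not give them.** Mean RR 15/min with between-person SD 3; breath-interval CV 20% (range 10–30%); lag-1 correlation of intervals 0.2 (0.6 as a check); a 60 s count starting at the sampling time; a patch that reports either unsmoothed breath-to-breath RR or a trailing 60 s average.

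**Breaths per window** = RR × seconds / 60. At an assumed 12–20/min:
- 5 s: 12 × 5/60 = 1.0 to 20 × 5/60 = 1.7
- 30 s: 6 to 10
- 60 s: 12 to 20

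**Resting agreement.** Breath-level simulation, 4,000 records per scenario. Limits of agreement are ±1.96 × SD of (patch − count), in breaths/min. For a single point at CV 20%, 1.96 × 3.29 = 6.45.

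| Patch value | CV 10% | CV 20% | CV 30% | r at CV 20% |
|---|---|---|---|---|
| Single point, unsmoothed | ±3.20 | ±6.45 | ±9.87 | 0.67 |
| 5 s window, unsmoothed | ±2.65 | ±5.26 | ±7.93 | 0.75 |
| 30 s window, unsmoothed | ±1.30 | ±2.22 | ±3.37 | 0.94 |
| Single point, patch averages 60 s | ±1.54 | ±2.75 | ±3.92 | 0.91 |
| 30 s window, patch averages 60 s | ±1.36 | ±2.34 | ±3.31 | 0.93 |
| Rate over exactly the counted minute | ±0.82 | ±0.91 | ±1.03 | 0.99 |

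With lag-1 correlation 0.6 at CV 20%, the rows become ±6.27, ±5.56, ±2.82, ±4.02, ±3.39 and ±0.88. An error-free patch against error-free capnography in the same window differs by 0 by construction.

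**After exertion.** Suppose RR is A above rest until the movement ends, then the excess decays with time constant 40 s, and a 60 s count starts at the end. These values are assumed. As fractions of A:
- Mean excess in the counted minute: (40/60)(1 − e^(−60/40)) = 0.518
- Single point at the start: 1 − 0.518 = 0.482 bias
- 30 s window centred on the end: [1 + (40/15)(1 − e^(−15/40))]/2 − 0.518 = 0.917 − 0.518 = 0.399
- 30 s window starting at the end: (40/30)(1 − e^(−30/40)) − 0.518 = 0.704 − 0.518 = 0.186
- Matched minute, unsmoothed patch: 0
- Patch with trailing 60 s average, read at the start: 1 − 0.518 = 0.482
- The same patch, averaged over the counted minute: [30 + 40 − 40 × 0.518]/60 − 0.518 = 0.821 − 0.518 = 0.303

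For A = 4 to 8/min, a single point is biased by +1.9 to +3.9/min, the centred 30 s window by +1.6 to +3.2 and the forward 30 s window by +0.7 to +1.5. Matching removes this for an unsmoothed patch. For a patch averaging over 60 s, +1.2 to +2.4 remains, which is the device's own lag.

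**The case against.** The strongest reply is that the affected comparison is a supporting one. Capnography is the gold standard, it is continuous, and it is the RR comparator named in the secondary outcome. Device selection is also tied to closeness to the gold standard, and RR has no part in the primary outcome. This stands, and it limits the consequence. It does not remove the manual comparison, which the objectives and the paired-reading rule both call for.

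A reader might infer that even a perfect patch must agree poorly with the count. The documents do not support that. The large figures need a single point or a very short window from an unsmoothed patch, and the article does not give the patch's averaging time. At 30 s, which the rule allows, r is 0.90 to 0.98 across the assumed CVs.

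A reader might also infer that the movement results will carry a known positive bias. That rests on an assumed RR rise, an assumed decay and a count starting exactly when the movement stops. Of the six tasks in Table 2, only repeated standing is clearly exertional; the others are mainly hand and arm tasks done seated.

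A third inference is that Stage 1 has no capnography, because its recording is described only for Stage 2. The secondary outcome calls for capnography-derived RR during movement, so its absence cannot be concluded.

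Two further replies have some force. The words per minute may give the unit rather than the counting time, and a shorter count would shrink the mismatch. Signal-specific pairing may also be refined in an analysis plan not shown. But the article does not leave the sampling open: it fixes one rule for all continuous signals, and that rule does not fit this pair.

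**Conclusion.** The concern holds in limited form. If the observer counts for a full minute, neither permitted sample covers the counted interval, and the patch-versus-manual statistics can include variation that is not device error. At an assumed interval CV of 20% with an unsmoothed patch, the limits widen from about ±0.9/min to ±2.2 at 30 s, ±5.3 at 5 s and ±6.5 for a single point. The size depends on breathing variability and on the patch's internal averaging, neither of which the article states. Bias after exertion is possible in the same comparison, but its size is conditional on assumed recovery values. The comparison with capnography in a shared window is unaffected. The plan should be changed because the correction is cheap, but the problem threatens neither the primary outcome nor the RR comparator named in the secondary outcome.

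**What to change.** In the Analysis section, exempt patch RR against the manual count from the single-point and 5–30 s rule. Pair each count with the mean patch RR over the same counted interval, and time-stamp the start and end of the count in the existing app, which already records study activities. For patch against capnography, apply any common window to both signals and treat this as the main RR comparison; a 60 s window is not needed there.

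The cost is one sentence in the plan and the start and end stamps for each count, by staff already present. Two limits remain. RR changes within the counted interval cannot be resolved, and any lag from the patch's own averaging stays in the comparison.
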